### 2.2. Randomization

#### 2.2.1. Randomization Sequence Generation

Eligible participants who provide informed consent after the baseline visit will be randomized and assigned in a 1:1 ratio to one of the two intervention groups, stratified by site. Randomization will be conducted using a computerized, web-based system called Interactive Response Technology (IRT). This approach ensures a balanced distribution of key covariates across the study sites. The centralized IRT system will generate the allocation sequence and assign the code corresponding to either active or sham rTMS. The study coordinator will implement the allocation specified by the IRT system.

Each site’s delegated physician or clinical research investigator will discuss the trial information with participants and obtain and document informed consent. Prior to any study visit or procedure, participants willing to participate will receive comprehensive information about the study and complete the informed consent process. During the screening visit, participants will have at least 24 h to review the study information before providing consent. After verifying eligibility criteria and obtaining informed consent, investigators will enroll the participants in the study and proceed with randomization.

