### 2.10. Sample Size Calculation

Due to the study design, the primary outcome will be evaluated by a two-sided *t*-test after 6 weeks of treatment. Values from Jahanbakhsh et al. [43] were used for sample calculations, namely Y-BOCS values of 27.40 ± 4.91 (control) and 27.53 ± 4.61 (treatment) at baseline and 27.33 ± 4.15 (control) and 24.07 ± 4.35 (treatment) post-treatment. Performing the sample size calculation (STATA BE 17.0) with an alpha of 0.05 and a power of 0.9, to reduce the type II error, estimated a size of 76 participants. Due to the low adverse events in rTMS, it has a low dropout rate, from 5.3% in active use to 11.28% in sham use [44]. Additionally, the OCD patient cohort has a various dropout rate, from 17.29% in pharmacological trials, over 20.63% in active control like metacognitive therapy, to 23.49% in pill placebo [45]. Considering these two, we aim for a 30% dropout rate to ensure we do not lose power during the trial. Thus, our calculation leads to 110 participants overall, with a sample size of 55 participants per group.

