### 2.11. Statistical Analysis for Primary and Secondary Outcomes

Baseline characteristics will be presented as frequencies with percentages for categorical data, or means ± SD for data with normal distribution, respectively, and medians with interquartile range (IQR) for data with non-normal distribution. Statistical analyses will be evaluated as intention-to-treat. The primary endpoint of Y-BOCS as an ordinal variable on a 40-point Likert scale will be analyzed using a *t*-test [46] and Mann–Whitney-U test, respectively, and will be adjusted to sex, depression, and baseline severity of OCD with multiple regression. Normality will be assessed using the QQ-Plot and Kolmogorov–Smirnov test.

Secondary endpoints of response rate measured by Y-BOCS will be assessed in percentages, and significance will be calculated using Fisher’s exact test. Time-to-response analysis will be conducted using the Kaplan–Meier probability.

Overall Sheehan Disability score and Hamilton Depression Rating Scale (HDRS) will be tested. 55-point Likert scales will also be analyzed using a *t*-test, respectively Mann-Whithney-U in case of non-normality distribution. The Sheehan Disability score will be compared for the three individual scores (work, social life, family life) and multiple comparison corrections via the Benjamini Yekutieli procedure. The Mann-Whitney-U test will analyze Clinical Global Impression Scales on a 7-point. Finally, the fMRI study will use the Amplitude of Low-Frequency Fluctuations (ALFF) and regional homogeneity (ReHo) analysis [47] to determine differences in the function of the brain after rTMS.

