### Limitations

Despite its strengths, the study has some limitations that must be acknowledged. First, it is a theoretical study and has not been implemented into a study. Further the national multicentric design introduces demographic diversity, which enhances generalizability but may also lead to variability that complicates data analysis. Additionally, differences in standard care practices, such as the implementation of cognitive-behavioral therapy across centers, could influence outcomes and serve as potential confounding factors. The intensive six-week treatment regimen may pose logistical challenges for participants, potentially resulting in higher dropout rates and affecting the study’s retention. Furthermore, the absence of a long-term follow-up period limits the ability to assess the sustained efficacy and durability of rTMS treatment effects. These limitations should be considered when interpreting the study results and highlight areas for future research.

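### Site is the only stratification factor named, yet the fixed covariate list omits it: a small, avoidable loss of precision if site is prognostic

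*Protocol article*

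**What the plan says.** Section 2.2.1 of the protocol article has participants "randomized and assigned in a 1:1 ratio to one of the two intervention groups, stratified by site". No other stratification factor is named.

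Section 2.11 compares Y-BOCS by t-test or Mann–Whitney U and says that the comparison "will be adjusted to sex, depression, and baseline severity of OCD with multiple regression". The secondary endpoints are assigned Fisher's exact test, Kaplan–Meier, t-tests and Mann–Whitney tests. Site appears in none of these, nor in section 2.12 on missing data. The sample size in section 2.10 rests on a two-sided t-test at 6 weeks, "with an alpha of 0.05 and a power of 0.9", again without a site term.

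The Limitations say that the multicentre design "may also lead to variability that complicates data analysis" and that "differences in standard care practices, such as the implementation of cognitive-behavioral therapy across centers, could influence outcomes and serve as potential confounding factors".

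**The concern.** When allocation is balanced within site, differences between sites cancel out of the treatment comparison. An analysis that ignores site still counts those differences as error. Its standard error is then larger than the true one, the test rejects too rarely under the null, and some power is given away.

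The article restricts randomisation on site and says that centre practice may matter for outcome. It then leaves site out of an explicit list of covariates. What is at stake is efficiency and an interval of the right width, not validity. Settling the matter now also avoids a later choice between site-adjusted and unadjusted results.

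**Working it through.** **Inputs from section 2.10.** Post-treatment Y-BOCS is 27.33 ± 4.15 (control) and 24.07 ± 4.35 (treatment); alpha is 0.05 two-sided, power 0.9, 76 evaluable (38 per arm), 30% dropout, 110 recruited.

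**Assumptions.** The documents give neither the number of sites nor the share of outcome variance due to site (ICC). I take 6 to 8 sites and ICC 0.02 to 0.20. The relevant ICC is the residual one, after the covariates already listed.

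**The plan's own figure.**
- Difference: 27.33 − 24.07 = 3.26.
- Pooled SD: √((4.15² + 4.35²)/2) = 4.251, so d = 3.26/4.251 = 0.767.
- Normal formula: 2(1.960 + 1.282)² × 4.251²/3.26² = 35.7, so 36 per arm. The noncentral t gives 37 per arm (74 in all). At 38 per arm, power is 91.0%. The stated 76 is reproduced to within 2 patients.
- Dropout: 76/0.7 = 108.6, so 109, or 110 for equal arms. This is also reproduced.

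**Effect of omitting site, arms balanced within site.** The nominal SE at 38 per arm is 4.251 × √(2/38) = 0.975, so the noncentrality is 3.26/0.975 = 3.343. The critical t on 74 df is 1.993.
- SE overstatement: 1/√(1 − ICC).
- Power without site: Φ((3.343 − 1.993)/√(1 − ICC)).
- Power with site as a fixed effect: noncentral t with noncentrality 3.343/√(1 − ICC) and 74 − (sites − 1) df.
- If site variance comes on top of the SD of 4.251, power without site: Φ(3.343 − 1.993/√(1 − ICC)). Power with site stays at about 90.9%.

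For example, at ICC 0.10 power without site is Φ(1.350/0.949) = Φ(1.423) = 92.3%. With site variance on top it is Φ(3.343 − 2.100) = 89.3%.

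| Residual ICC | SE ratio | Power without site | Power with site | Gain (points) | Power without site, site variance on top |
|---|---|---|---|---|---|
| 0.02 | 1.010 | 91.4% | 91.4–91.5% | about 0 | 90.8% |
| 0.05 | 1.026 | 91.7% | 92.2% | 0.5 | 90.3% |
| 0.10 | 1.054 | 92.3% | 93.5% | 1.2 | 89.3% |
| 0.20 | 1.118 | 93.4% | 95.8% | 2.3 | 86.8% |

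Six and eight sites agree to the rounding shown.

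**Simulation, balanced within site** (5 and 10 sites, 4,000 runs, 38 per arm). At ICC 0.10 the unadjusted test rejected a true null in about 3.8% of runs, against 4.7% with site in the model. At 0.20 the figures were about 3.6% and 5.4%. The Monte Carlo error is about √(0.05 × 0.95/4,000) = 0.3 points. Simulated power at ICC 0.20 was 93–94% without site and 95–96% with it.

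**Simulation, no blocking within site** (6 sites, 6,000 runs). Unadjusted rejection of a true null was 4.5%, 4.5% and 5.2% at ICC 0.05, 0.10 and 0.20, which is close to nominal. With no site effect at all, power was about 90.6% without and 88.7% with fixed site effects. With 20 sites of about 4 patients it was about 90% and 80%.

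**The case against.** *Left to the SAP.* A journal article condenses, and silence on site would be no finding. But the article is not silent: it lists three covariates and leaves out the factor it stratifies by. This defence only partly stands.

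*Size.* At the plan's own inputs the gain is at most about 2.5 points over the assumed range and nothing at an ICC of 0.02 or below. Baseline severity and depression are already in the regression and may absorb part of any site variance. This stands, and it makes the point one of efficiency.

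*Balance.* Section 2.2.1 does not describe blocks or minimisation. Without them, the unadjusted test has close to its nominal size. So the conservatism is conditional on within-site balance, which stratification normally aims for but the article does not spell out.

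Three stronger readings are tempting, and the documents do not support them.
- A reader might infer that the trial is underpowered. Unadjusted power stays above 90% unless site variance adds to the planning SD, and the documents do not say whether it does.
- A reader might take from the word confounding in the Limitations that omitting site biases the comparison or inflates false positives. Site-stratified allocation already largely prevents confounding by centre; a site term mainly adds precision.
- A reader might infer that the plan expects site effects. It says only that care differences could influence outcomes.

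**Conclusion.** The point holds as a modest efficiency recommendation. Site is the only stratification factor named, the article itself treats it as possibly prognostic, and the stated covariate list omits it. If site is prognostic and arms are balanced within site, the standard error is overstated by about 1% to 12%, and between 0 and about 2.5 power points are given away, over an assumed residual ICC of 0.02 to 0.20 with 6 to 8 sites. Power falls below the planned 90% only if site variance is additional to the planning SD and the ICC is about 0.10 or more. The validity of the primary comparison is not in question.

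**What to change.** In section 2.11, add site to the multiple regression for Y-BOCS and make that model the primary analysis; otherwise the site term does not reach the t-test named in section 2.10. Use fixed site effects if there are few sites of reasonable size, or a random intercept if there are many small ones. State beforehand how very small sites are pooled.

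For the secondary endpoints, use site-stratified or site-adjusted versions only where site sizes allow. Fisher's exact test, Mann–Whitney and Kaplan–Meier take no covariates, and stratified versions become sparse in small sites.

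Reword the limitation: under site-stratified allocation, centre differences in care are mainly a matter of precision, and a site main effect does not address differences in treatment effect between sites.

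The cost is a sentence or two of text and a few degrees of freedom. If site turns out not to be prognostic, the loss is a fraction of a power point under balanced allocation and about 2 points with 6 unblocked sites. Fixed effects for many very small unblocked sites would cost far more (about 10 points in the 20-site simulation), which is why the pooling rule or random intercept belongs in the plan.

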#### 2.8.2. Secondary Outcome Measures

Secondary outcomes include the difference in response rate and the time-to-response between the groups. The response rate will be measured as a dichotomous variable to quantify the patients who achieve clinically significant improvements. A complete and partial response rate will be defined as a reduction of ≥35% in the Y-BOCS score [36]. The latter will be defined as the time at which a partial response of a reduction of ≥25% in the Y-BOCS score will be seen.

In addition, the Clinical Global Impression (CGI) scale will be used by an experienced psychiatrist to measure the global judgment of improvement or worsening. During the assessment of the CGI scales, the psychiatrist will judge the illness severity, the patient’s level of distress, and the impact on daily functioning [37]. Moreover, the Sheehan Disability Scale (SDS) will measure the degree of disability of the patient. The SDS is a three-item self-rate scale that provides insights into the level of impairment in work, social, and family functioning [38]. We will also measure self-reported improvement in symptoms of obsessions and compulsions utilizing the Padua Inventory (PI) [39]. Lastly, patients with OCD often have depression, which could be a significant moderator of the efficacy of TMS in these patients [40]. We will measure the depressive symptoms using the widely validated Hamilton Depression Rating Scale (HDRS). The HDRS 17-item clinician-administered tool is used to measure depressive symptoms [41]. All scales will be evaluated at baseline in two, four, and six weeks.

OCD patients display abnormal regional homogeneity (ReHo) in functional MRI (fMRI) in the right dlPFC region [42]. Therefore, an additional fMRI will be conducted during the baseline MRI to localize the right dlPFC. After 6 weeks of treatment, we will assess the post-treatment fMRI.

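### For the three Sheehan sub-scores, Benjamini-Yekutieli is valid but needlessly conservative; Holm keeps 5% family-wise control under any dependence and usually gains a few points of power.

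*Protocol article*

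**What the plan says.** The protocol article makes the Sheehan scale a secondary outcome (2.8.2) and describes it as a "three-item self-rate scale that provides insights into the level of impairment in work, social, and family functioning". Section 2.11 first says that the overall Sheehan score will be tested. It then says that the scale will be "compared for the three individual scores (work, social life, family life) and multiple comparison corrections via the Benjamini Yekutieli procedure".

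The method is therefore fixed by name and is not left to a later analysis plan. The article gives no reason for the choice, no error rate that the correction should control, and no separate level for this family. The only level stated is in the sample size section (2.10), "with an alpha of 0.05 and a power of 0.9", and it belongs to the primary outcome.

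**The concern.** Benjamini-Yekutieli takes the Benjamini-Hochberg cut-offs and divides them by 1 + 1/2 + 1/3 = 1.833, so that the guarantee holds under any dependence, including adverse dependence. With only three tests this is a heavy penalty. If one sub-score alone responds, it must in effect reach p ≤ 0.0091, where a plain Bonferroni correction would ask for 0.0167.

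Other procedures for three tests keep family-wise error at 5% and demand less of the data. The trial is sized on Y-BOCS only, so the Sheehan items have no planned power in reserve. What is at stake is some chance of showing which area of functioning improved: work, social life or family life.

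**Working it through.** **Inputs.** Three tests (2.11). Level 0.05, two-sided: assumed for this family, because 2.10 states it only for the primary outcome. Patients per arm: 38 (76 evaluable) or 55 (110 randomised), both from 2.10. Sheehan effects and correlations are not in the article, so effects of 0.3 to 0.6 SD and correlations of 0.3 to 0.7 are assumed.

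**The plan's own figures.** The article gives no cut-off or power for the Sheehan items. Its sample size does reproduce closely. A difference of 27.33 − 24.07 = 3.26 with a pooled SD of about 4.25 needs 37 per arm (74) by the exact t calculation, and 38 per arm gives power 0.910. Then 76/0.70 = 108.6, so 109, or 110 for equal arms. Both 38 and 55 are fair inputs.

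**Cut-offs, smallest to largest p-value.** Benjamini-Yekutieli: i × 0.05/(3 × 1.833). Holm and Hochberg: 0.05/(3 − i + 1).

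| Step | Benjamini-Yekutieli | Holm and Hochberg |
|---|---|---|
| 1 | 0.0091 | 0.0167 |
| 2 | 0.0182 | 0.0250 |
| 3 | 0.0273 | 0.0500 |

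Hochberg and Benjamini-Yekutieli both step up, so Hochberg rejects everything that Benjamini-Yekutieli rejects. Holm steps down, so it does not dominate in every pattern.

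- p = 0.012, 0.030, 0.040: Benjamini-Yekutieli rejects 0, Holm 1, Hochberg 3.
- p = 0.02, 0.02, 0.02: Benjamini-Yekutieli rejects 3, Holm 0, Hochberg 3.

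**Worst-case family-wise error under any dependence.** Set the p-values of false nulls to 0. For a step-up procedure with cut-offs c1, c2, c3 the worst case is:

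- 3 true nulls: 3 × [c1 + (c2 − c1)/2 + (c3 − c2)/3]
- 2 true nulls: 2 × [c2 + (c3 − c2)/2]
- 1 true null: c3

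For Benjamini-Yekutieli with 3 true nulls: 3 × (0.00909 + 0.00455 + 0.00303) = 0.0500. For Hochberg: 3 × (0.01667 + 0.00417 + 0.00833) = 0.0875. A linear programme over joint p-value distributions gives the same values.

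| True nulls | Benjamini-Yekutieli | Holm | Hochberg |
|---|---|---|---|
| 1 | 0.0273 | 0.0500 | 0.0500 |
| 2 | 0.0455 | 0.0500 | 0.0750 |
| 3 | 0.0500 | 0.0500 | 0.0875 |

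**Power.** Three equicorrelated normal statistics with mean d × √(n/2), 400,000 draws per scenario. With 38 per arm, d = 0.5 on all three items and correlation 0.5:

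| | Benjamini-Yekutieli | Holm | Hochberg |
|---|---|---|---|
| Power per item | 0.417 | 0.481 | 0.502 |
| At least one rejection | 0.591 | 0.666 | 0.678 |

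Over the assumed ranges, the gain per affected item over Benjamini-Yekutieli is:

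- Holm, two or three items affected: about 3 to 7 points.
- Holm, one item affected: about 4 to 8.5 points.
- Hochberg, all three affected: about 5 to 9 points.

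With one affected item, d = 0.5 and 38 per arm, the chance of any rejection rises from about 34.5% to about 43%, close to 9 points. A hand check for the item itself: the mean is 0.5 × √19 = 2.18. The critical values for 0.0091 and 0.0167 are 2.61 and 2.39, so power is Φ(−0.43) = 0.33 against Φ(−0.21) = 0.42.

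**Realised error when nothing works**, correlations 0.3 to 0.7: Benjamini-Yekutieli 2.7% to 2.4%, Holm 4.8% to 3.9%, Hochberg 4.8% to 4.1%. Benjamini-Yekutieli rejected more than Holm in at most about 0.15% of draws.

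**The case against.** The strongest defence is that the plan names a valid, conservative method that needs no dependence assumption, for three sub-items of a secondary endpoint in a phase II trial. That stands: nothing in 2.11 is false, and type I error is controlled. Four stronger criticisms are tempting and fail.

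- A reader might infer that the plan settles for the weaker false discovery rate. That is the general guarantee of the method. With three tests its cut-offs also hold family-wise error at 5% under any dependence, as the table shows.
- A reader might infer that the penalty buys no protection. Against Hochberg it does, since Hochberg can reach 0.0875 under adverse dependence. Three items of one scale in the same patients are plausibly positively correlated, which makes this protection less needed. The article gives no correlation, so it cannot be called worthless.
- A reader might infer that changing costs no error. The realised null rate rises from about 2.5% to between 4% and 5%. It stays within the level, but it rises.
- A reader might infer that the whole disability outcome loses power. Section 2.11 tests the overall Sheehan score as well, and the correction is attached only to the three individual scores.

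The defence does not answer the comparison with Holm, which gives family-wise control at the same 5% under the same absence of assumptions, with higher average power. Holm is not uniformly better, as equal p-values of 0.02 show, but such patterns are rare.

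**Conclusion.** The point holds as a matter of efficiency and not of validity. For three Sheehan sub-scores at 0.05, Benjamini-Yekutieli is stricter than family-wise control under any dependence requires in nearly all patterns. Against Holm it gives up about 3 to 7 points of power per item when two or three items respond, and up to about 9 points when only one does. These sizes rest on assumed effects, assumed correlations and an assumed 0.05 for this family. The cut-offs and worst-case errors need only the last of these. The consequence is minor: the primary outcome and the overall Sheehan test are untouched.

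**What to change.** In 2.11, for the three Sheehan sub-scores, replace the named procedure with the Holm procedure at two-sided 0.05, and say that it controls family-wise error across these three tests. Hochberg is an alternative only if the authors are willing to state and defend positive dependence among the items.

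The cost is one phrase and a different software option, with no patients and no new data. The authors accept a realised null error closer to, but still within, 5%, and rare patterns in which Holm rejects less than the present method. The article describes the study as hypothetical and not yet implemented, so the change can be made before any data exist.

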### 2.12. Missing Data

Missing data will be assessed for each variable. Multiple imputations will be used for primary and secondary endpoints and other potential missing data. In all cases, the model fit will be assessed visually via density plots indicating the distributional discrepancy, i.e., the difference between observed and imputed data.

### 2.13. Ethical Considerations

This study will follow the Ethical Principles for Medical Research Involving Human Subjects and Good Clinical Practice outlined in the Declaration of Helsinki and be considered for ethical approval by the Institutional Review Board Committee at each local site. We intend to register this study in the Clinical trial register under clinicaltrials.gov. Before participating in this trial, each participant will be fully informed about all aspects of the trial, including the experimental procedures, and give written informed consent, and each enrolled patient will receive a copy of the informed consent form.

The investigators are responsible for recording and reporting all serious adverse events (SAEs) that occur throughout the research protocol, starting from the time consent is obtained and continuing through the entire monitoring period. SAEs will be documented using a comprehensive form designed for this purpose, which must be completed, printed, dated, signed, and promptly communicated to the principal investigator. Regardless of when they occur during the protocol, any SAEs suspected to result from the research protocol, where no other reasonable explanation exists, must also be reported.

Adverse events (AEs) that do not meet the criteria for SAEs will be documented only on the patient’s medical card, including details such as the date of onset, characteristics, intensity, duration, possible causes, actions taken, treatments administered, and outcomes. At each evaluation, the investigator will assess whether any AEs or SAEs have occurred and will record all such events on the appropriate case report form (eCRF) page. For each event, the nature, severity, and relationship to the study protocol or treatment will be documented.

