However, this approved alternative is for deep TMS and, therefore, requires a specific coil to stimulate deep brain areas, which limits its availability in a wide real-world setting [19]. Our theoretical trial will focus on rTMS, as the needed coils will be more available. While different targets are potentially effectual, the right dlPFC seems the most effective in the general OCD population [15,20]. Unfortunately, conflicting evidence exists in treatment-resistant patients [21]. Moreover, the standard assessment of the optimal localization of stimulation of the dlPFC lacks accuracy. A study by Zhang et al. found that the dlPFC, assessed by the 5 cm rule, was meticulous in 13.8% to 54% [22]. Therefore, there is a need for an MRI-based neuronavigation to localize the dlPFC exactly individually to reduce side effects in other areas and improve the efficient investigation of treatment in this area.

Consequently, this theoretical trial seeks to determine the efficacy and safety of low-frequency repetitive transcranial magnetic stimulation (LF rTMS) applied to the right dorsolateral prefrontal cortex (dlPFC) in conjunction with standard therapy for treatment-resistant Obsessive–Compulsive Disorder (OCD) in adults. The hypothesis postulates that the rTMS protocol will result in a statistically significant reduction in Yale-Brown Obsessive Compulsive Scale (Y-BOCS) scores compared to a sham intervention in patients undergoing standard therapy over 6 weeks.

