### 2.9. Data Management

#### 2.9.1. Data Monitoring

An independent Data Monitoring Committee (DMC) of external experts in the area, without conflict of interest relevant to this study, will be established. The DMC will assess the progress, safety data and, if needed, critical efficacy endpoints. Confidentiality will be maintained during data monitoring, review, and deliberations. The Project Officer (PO) and the DMC will develop meeting agendas. Voting and minutes will be kept confidential. Open Session and Close Section reports will be prepared, presented, and appropriately distributed. Recommendations on the trial’s continuity, pause, or termination and necessary adjustments will be tracked to ensure prompt and effective implementation.

All data will be entered electronically in the trial. The original study forms will be entered and kept on file at the participating sites. The Clinical Data Management System (CDMS) will handle the data. At every visit, an electronic version of the Case Report Form (e-CRF) will be applied to all participants. The collected data from the participating sites will be sent to the Core Coordinating Center.

The entries of the e-CRFs will be monitored by the Clinical Research Associate (CRA) for completeness, and filled-up CRFs will be retrieved and handed over to the Clinical Data Management (CDM) team. The CDM team will track the retrieved CRFs and maintain their record. An Edit Check Program will be developed to detect discrepancies after validation with dummy data. In the case of data discrepancy, a Data Clarification Form (DCF) will be generated and delivered to the responsible investigator, who will have 48 h to resolve the issue. To enforce the data integrity, the CDM team will review all discrepancies regularly to ensure they have been resolved. There will be a discrepancy database where all discrepancies will be recorded and stored with an audit trail.

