#### 2.9.2. Interim Analysis

During the interim analysis for adverse effects at 3 weeks, a Data and Safety Monitoring Board (DSMB) will ensure patient safety and determine the continuation of the trial. The DSMB will compare the rate of adverse effects, especially serious events like seizures, between the groups. Because there will be no interim statistical analysis, there is no need for alpha spending function adjustments.

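### Section 2.13 gives two incompatible rules for where non-serious adverse events are recorded, so these data could be incomplete or differ by site

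*Protocol article*

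**What the plan says.** Section 2.13 (Ethical Considerations) of the protocol article deals with event recording in three steps.

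- **Serious events.** "SAEs will be documented using a comprehensive form designed for this purpose". The form is signed and goes promptly to the principal investigator.
- **Non-serious events.** "Adverse events (AEs) that do not meet the criteria for SAEs will be documented only on the patient’s medical card". The sentence then lists what the card is to hold: date of onset, characteristics, intensity, duration, possible causes, actions, treatments and outcome.
- **Both classes.** The very next sentence has the investigator check for AEs and SAEs at each evaluation and says that he or she "will record all such events on the appropriate case report form (eCRF) page". It is followed by: "For each event, the nature, severity, and relationship to the study protocol or treatment will be documented".

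Three other places bear on this. Section 2.9.1 (Data Monitoring) states: "All data will be entered electronically in the trial", with an eCRF at every visit and site data sent to a coordinating centre. Section 2.9.2 (Interim Analysis) states: "The DSMB will compare the rate of adverse effects, especially serious events like seizures, between the groups". The Introduction makes safety part of the aim: the "theoretical trial seeks to determine the efficacy and safety of low-frequency repetitive transcranial magnetic stimulation".

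**The concern.** The second step names the medical card as the sole place for a non-serious event. The third step puts the same event on the eCRF. These are two stated rules that disagree. This is not a detail left to a fuller document.

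The trial is multicentre, and its database is built from what sites enter. If some sites take the card rule literally, their headaches, muscle twitching and hearing complaints stay in local records, while other sites report theirs. The pooled non-serious AE counts would then depend partly on which sentence a site followed. At stake are the tolerability half of the safety aim and the non-serious part of the comparison the DSMB is asked to make.

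**Working it through.** The protocol gives no figure to reproduce on this point. The check is a comparison of texts, followed by two short calculations that show what is and is not at risk.

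**1. The rules side by side, by type of event**

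| Event type | SAE form | Medical card | eCRF |
|---|---|---|---|
| SAE | yes (2.13) | not stated | yes (2.13, each evaluation) |
| Non-serious AE, card sentence | not mentioned | yes, and nowhere else | excluded |
| Non-serious AE, eCRF sentence | not mentioned | not mentioned | yes |

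The last two rows contradict each other in the eCRF column. Section 2.9.1 sides with the last row, since it has all data entered electronically. The SAE row contains no conflict.

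**2. The details side by side**

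- Assigned to the card: onset date, characteristics, intensity, duration, possible causes, actions, treatments, outcome.
- Named for each event after the eCRF sentence: nature, severity, relationship.

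Even a site that obeys both sentences finds onset, duration and outcome named for the card alone. Onset dates matter for a safety review placed at 3 weeks.

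**3. What a mixed practice would do to the comparison**

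Assume that a share *f* of patients is at sites using the card alone, that *f* is the same in both arms, and that true event risks *p₁* (active) and *p₀* (sham) do not vary by site. Equal *f* is reasonable because section 2.2.1 stratifies the 1:1 randomisation by site. Then:

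- recorded risk in each arm = (1 − *f*) × true risk;
- recorded risk difference = (1 − *f*) × (*p₁* − *p₀*).

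At *f* = 0 nothing is lost. At *f* = 1 no non-serious event reaches the database. In between, absolute rates are understated and the difference shrinks in proportion. The documents give no basis for choosing *f*, so this range is all that can be stated.

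**4. How much serious events alone could say**

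Inputs: 55 patients per arm (sections 2.5 and 2.10); 5 sessions a week for 6 weeks, so 30 sessions (2.7.1); seizure risk 8 per 100,000 sessions (2.7.2, Seizures).

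- Active sessions: 55 × 30 = 1,650.
- Expected seizures: 1,650 × 8 / 100,000 = 0.132, about 0.13 in the whole active arm.

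The event that section 2.9.2 singles out will most likely not occur. The figure covers seizures only. Section 2.3.2 lists other severe events (neurological deficits, manic or psychotic symptoms, suicidality) for which the article gives no rates, so 0.13 is not the expected number of SAEs.

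**The case against.** The strongest reply is that the contradiction is one loose word. The card sentence comes directly after the paragraph on the SAE form and can be read as its contrast: a non-serious event needs an ordinary source note and no special form. The eCRF sentence then covers both classes, section 2.9.1 agrees with it, and no data are lost. This reading is plausible and may well be what was meant. But the text does not say it. It names a place of documentation, excludes others, and gives that place a full set of data items. A site coordinator could fairly follow it literally.

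Two further replies stand in full. SAEs have their own form and the eCRF, so the serious events stressed in section 2.9.2 are captured under either rule. Depressive worsening is also protected, because the HDRS is a scheduled measure at baseline and weeks 2, 4 and 6 (section 2.8.2).

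A reader might infer that the trial, followed as written, cannot meet its safety objective or supply the DSMB comparison. The documents do not support that. As written, they also order every AE onto the eCRF, and the loss arises only where a site follows one sentence and ignores the next. Nor does 0.13 expected seizures show that nearly all comparative safety information is non-serious, since other serious events are left out of it.

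**Conclusion.** The point holds as a contradiction between adjacent sentences that should be removed before sites are trained. Its consequence is limited: non-serious AE data could be incomplete or differ between sites, which weakens the safety aim and the non-serious part of the DSMB's comparison. SAE capture, the primary endpoint, the error rate and the power are untouched.

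The size cannot be fixed from the documents. It runs from no loss, if every site enters all events on the eCRF, to no non-serious events in the database, if every site uses the card alone. With mixed practice and the assumptions stated in the working, the likely effect is under-counting and a diluted difference. A systematic tilt towards one arm is not implied. How AEs are tabulated by arm is commonly left to documents not shown, and its absence is not part of this point.

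**What to change.** In section 2.13, delete *only* from the sentence on non-serious AEs, or state that it means no SAE form is needed for them. Then require every AE and SAE to be entered on the eCRF AE page that the section already mentions, and add the onset, duration and outcome items now assigned to the medical card to the nature, severity and relationship already named. The card can stay as the source record.

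The cost is a sentence of text, a few more fields on an existing page, and slightly more data entry at sites. The change concerns data capture only and alters no treatment or clinical rule. It is cheap before enrolment, whereas events not collected uniformly are hard to recover afterwards.
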